### Exclusion Criteria

Subjects meeting any of the exclusion criteria at baseline will be excluded from study participation.

1. Two oncologists disagree on prognosis or resectability.
2. Severe or uncontrolled medical disorder that would, in the investigator's opinion, confound study analyses of treatment response (i.e., uncontrolled diabetes, chronic renal disease, chronic pulmonary disease or active, uncontrolled infection, psychiatric illness/social situations that would limit compliance with study requirements).
3. Are pregnant or breast-feeding patients or any patient with childbearing potential not using adequate pregnancy prevention (site-specific criteria applying to Avera only).

## 3.0 Study Plan

### Study Overview

[figure not shown]

[figure not shown]

| Abbreviations |                     |
|---------------|---------------------|
| CR            | Complete response   |
| PR            | Partial response    |
| SD            | Stable disease      |
| PD            | Progressive disease |

[figure not shown]

## **Navigation to Treatment**

### **Study Groups**

Patients will be grouped into one of three study Groups (Groups 1, 2, or 3) based on their disease status and history of prior cancer therapy:

Group 1: Treatment naïve patients with unresectable disease or medically unfit for surgical resection.

Group 2: Treatment naïve patients with metastatic disease.

Group 3: Patients with metastatic or unresectable disease who have received at least one prior unmatched systemic therapy and no prior matched therapy.

### **Patient and Physician Participation**

Licensed and board-certified medical oncologists (who will also be sub-investigators on the study) treating patients with incurable malignancies with aggressive biology will have access to enrolling their patients in the trial. These patients will be offered one of the Foundation Medicine assays for tumor analysis. If a clinician chooses not to enroll a patient, the patient will not participate in the study even if he or she would have been otherwise eligible. Unless a practitioner chooses not to accrue patients, there will be no a priori selection for practitioners who already feel that the approach is feasible in their patient population. Every practitioner will have equal access to enrolling appropriate patients. Finally, it should be noted that this limitation applies to all trials at Moores Cancer Center and elsewhere. Physicians may always choose or not choose to enroll patients on a trial.

At the Avera McKennan site this will require a consultation to the Avera McKennan Precision Oncology clinic.

### **Tumor Profiling**

Patients who meet the eligibility criteria and provide consent will have their tumor and/or blood profiled via Foundation Medicine's FoundationOne™ and/or FoundationACT™ assays. Available tissue/blood will constitute an adequate biopsy for molecular testing in the metastatic setting. If the patient has not had intercurrent targeted therapy, an archived diagnostic tumor sample will suffice. If the patient has received targeted therapy (Group 3), all attempts will be made to acquire a post-treatment biopsy.[7] Previous studies have shown that, in the absence of intercurrent targeted therapy, archival tissue is adequate for molecular testing and that matched treatment based on results from archival tissue is associated with significantly higher than expected response rates.[6, 8] If an eligible patient has had their tumor profiled via Foundation Medicine's FoundationOne™ assay under the auspices of routine clinical care, but they meet all criteria for enrollment to I-PREDICT, they may be consented and enrolled.

If the sample is not able to be tested or fails testing, additional sections will be sent to Foundation Medicine. If re-testing fails, a repeat biopsy may be performed if clinically appropriate or the patient may receive traditional chemotherapy. We will not delay beyond 6 weeks while awaiting Foundation Medicine testing.

## **Determining Actionability of Genomic Abnormalities**

The process for determining actionability of genomic abnormalities relies upon the genomic alterations, mutant allele frequency, and diagnoses. This process remains in evolution. I-PREDICT assesses the combined approach of using a Molecular Tumor Board and the readings from Foundation Medicine to determine actionability, hence mimicking what practitioners would do in the community. Foundation Medicine readings are based on one of the largest databases available in the country, and include about 17,000 citations. This approach is identical to that in the IRB approved WINther protocol (approved at 6 sites, including USCD, and in 5 countries) which uses a clinical management committee as well as Foundation Medicine readings to ascertain genomic actionability. The current protocol uses the same methodology, except that the clinical management committee is called a molecular tumor board.

Alterations identified by the computational biology analysis are presented in the form of a variant report. Variant reports are routed to Foundation Medicine, Inc.'s proprietary content curation pipeline for report content compilation. Interpretive text for each alteration is prepared based on review of applicable scientific literature. The alteration interpretation addresses the following:

- Role of the affected gene in normal and tumor biology.
- Impact of the observed alteration on the function of the affected gene, if known.
- Prognostic implications of the alteration in the patient's tumor type, if any.
- Therapeutic implications of the alteration in the patient's tumor type, if any, including targeted therapies currently in development.

Foundation Medicine, Inc. also provides annotation that lists potential targeted therapies based on the genomic profile of the patient's tumor as follows:

- Targeted therapies for which the observed alteration implies either sensitivity or resistance in the patient's tumor type are listed, if available. Therapies are presented in separate groups based on their FDA approval status for the patient's tumor type. Only therapies that are FDA approved for at least one oncology indication are eligible to be listed in this report section.
- Literature references cited in support of interpretive text are included in the report bibliography.

In light of the aforementioned, we have adopted a process for defining actionability based upon a more systematic methodology. We will perform a classification similar to what is being done in germline genetic tests. This classification will include the following three-part definitions:

### **A. Significance Classification:**

- Deleterious: Mutation has been studied before and is known to be tumorigenic.
- Likely deleterious: Mutation is located in a known hotspot or functional domain.
- Variant of unknown significance: Variant is located in an unknown region or domain.
- Non-deleterious: Mutation is known to be non-tumorigenic.

### **B. Functionality Classification:**

- Loss of function (e.g., tumor suppressor gene).
- Gain of function (e.g., oncogene).
- Unknown

### **C. Actionability Classification:**

- Actionable: FDA-approved therapies exist in the patient's tumor type or another tumor type. Alternatively, a potential clinical trial exists at UCSD for which the patient may be a candidate based upon matched genomic alterations.

- Non-actionable: No FDA-approved therapies exist in the patient's tumor type or another tumor type. A potential clinical trial does not exist at UCSD for which the patient may be a candidate based upon matched genomic alterations.

\*Note: regarding equivocal copy numbers per FoundationOne™ assay reports:

- Amplified: An alteration denoted as “amplification – equivocal” implies that FoundationOne™ data provide some, but not unambiguous, evidence that the copy number of a gene exceeds the threshold for identifying copy number amplification. The threshold used in FoundationOne™ for identifying a copy number amplification is five (5) for ERBB2 and six (6) for all other genes. Specific gene amplifications or amplified chromosomal segments meeting this threshold will be considered for actionability.
- Loss: An alteration denoted as “loss – equivocal” implies that FoundationOne data provide some, but not unambiguous, evidence for homozygous deletion of the gene in question.

\*\*Note: regarding tumor heterogeneity

- Tumor heterogeneity is a biological limitation inherent to all treatments, whether matched or unmatched. Targetable mutations present in a minority of cells may not predict response in the same way that mutations in the dominant clone might. Sub-clonality will be considered on a case-by-case basis and combinations of matched therapies may be considered.

\*\*\*Note: regarding mutations and copy number changes of genes

- We will distinguish between mutations and copy number changes of genes. We agree that amplifications and deletions can include large territories and the targets of these events reported by Foundation Medicine may not be the relevant drivers of the disease. However, drivers from passengers cannot be reliably distinguished at this point of time; therefore, this feasibility study will be based on making decisions that are to the “best of our knowledge.”

\*\*\*\*Note: regarding genomic alterations with unclear functional significance

- Foundation Medicine analyses may reveal genomic alterations with unclear functional significance. As previously discussed, we will rely on expert opinion and literature review of the Study Committee or Molecular Tumor Board rather than a preconceived algorithm to assess the functional impact of a mutation. This will include location of the mutation in a functional domain, the level of amplification, consistency with assumed tumor suppressor functions or oncogenic role of a given gene, or published functional assessment of the mutation. Those alterations considered to be non-deleterious will not be targeted. In line with our methodology, we will not employ a computationally predicted deleterious score because an FDA-approved device for such decision-making does not exist.

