The current study will perform tumor molecular profiling through FoundationOne™ to navigate patients to a matched therapy at the discretion of their treating physician. For those patients with an actionable tumor alteration, matched therapy will be recommended by the Study Committee (or Molecular Tumor Board) from either FDA approved drugs or matched agents under investigation in a separate clinical trial. Those patients, for whom there are no available matched treatments, will serve as the unmatched therapy controls.

Patients with no actionable alterations by FoundationOne™ will be considered to have completed their participation in the study. Their basic data will be captured including demographics and tumor type and accounted into the denominator for feasibility analysis.

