#### **Secondary Endpoints:**

Determine the:

1. Proportion of patients that consent of all patients approached for the study
2. Time from informed consent to the receipt of FoundationOne™ genomic analysis
3. Proportion of patients with actionable genomic alteration
4. Proportion with insurance coverage for receiving molecularly targeted matched treatment based on genomic analysis

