### 7.2 Institutional Review Board (IRB) Approval and Consent

The IRB should approve the consent form and protocol prior to any study-related activities. It is expected that the IRB will have the proper representation and function in accordance with federally mandated regulations.

Avera Cancer Institute is conducting this trial under the purview of their local IRB. UCSD is not the IRB of record for Avera Cancer Institute.

In obtaining and documenting informed consent, the investigator should comply with the applicable regulatory requirement(s), and should adhere to Good Clinical Practice (GCP) and to ethical principles that have their origin in the Declaration of Helsinki.

Before recruitment and enrollment onto this study, the patient will be given a full explanation of the study and will be given the opportunity to review the consent form. Each consent form must include all the relevant elements currently required by the FDA Regulations and local or state regulations. Once this essential information has been provided to the patient and the investigator is assured that the patient understands the implications of participating in the study, the patient will be asked to give consent to participate in the study by signing an IRB-approved consent form.

Prior to a patient's participation in the trial, the written informed consent form should be signed and personally dated by the patient and by the person who conducted the informed consent discussion.

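### The trial route to actionability names UCSD alone, although a second site enrols patients and the matching rule accepts trials without a site limit

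*Protocol*

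**What the plan says.** Section 3.2, C. Actionability Classification, gives two routes to an actionable alteration. The first has no site limit: "Actionable: FDA-approved therapies exist in the patient's tumor type or another tumor type". The second does: "Alternatively, a potential clinical trial exists at UCSD for which the patient may be a candidate based upon matched genomic alterations". The non-actionable definition requires that no approved therapy exists and repeats the limit: "A potential clinical trial does not exist at UCSD for which the patient may be a candidate based upon matched genomic alterations".

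The Study Summary describes the study as multicenter. For the second site, Section 3.2 (Patient and Physician Participation) says: "At the Avera McKennan site this will require a consultation to the Avera McKennan Precision Oncology clinic". Section 4.1 (Molecular Profiling) sets out that site's own tissue handling, and Section 7.2 says: "Avera Cancer Institute is conducting this trial under the purview of their local IRB".

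The matching rule names no site. Section 1.2 has the Study Committee or Molecular Tumor Board recommend matched therapy "from either FDA approved drugs or matched agents under investigation in a separate clinical trial", and Section 3.2 (FDA-approved Companion Diagnostics) repeats this.

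The label has two uses. The third secondary endpoint in Section 1.5 is "Proportion of patients with actionable genomic alteration"; Section 6.5 reports it by group and for the whole population. Section 1.2 says that patients with no actionable alterations "will be considered to have completed their participation in the study", with basic data captured and the patient kept in the feasibility denominator.

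**The concern.** The classification is narrower than the matching rule that it feeds. The Board may recommend an agent in a trial open at the second site or elsewhere, while the classification does not count that trial. A patient with no approved drug in any tumor type, and such a trial as the only matched option, is non-actionable on paper although a matched therapy exists.

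Such a patient counts against the third secondary endpoint. If the exit in Section 1.2 is applied, participation also ends with little more than demographics and tumor type on record, so treatment, response and survival data may be lost. If it is not applied and the patient enters the local trial, the database holds a matched patient with a non-actionable tumor. Either way, a larger sample does not remove the error.

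**Working it through.** **Definition against matching rule.** No figure in the protocol depends on this wording, so there is none to reproduce. The check sets the rules side by side for a patient with no approved drug in any tumor type:

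| Only matched trial is open at | Section 3.2, C | Matching rule, Sections 1.2 and 3.2 |
|---|---|---|
| UCSD | Actionable | Eligible source |
| Second site, not UCSD | Non-actionable | Eligible source |
| Elsewhere | Non-actionable | Eligible source |

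The two rules disagree in rows 2 and 3. Row 3 can apply to a UCSD patient as well. A patient with an approved drug in any tumor type is classified alike everywhere.

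**What follows from the label.** Section 1.2 ends the participation of non-actionable patients. Section 3.2 (Molecular Matching and Molecular Tumor Board/Study Committee) says that patients with no actionable alterations receive the treating physician's choice of chemotherapy. The protocol does not say how these two statements fit together.

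**Link to the primary endpoint.** Sections 3.2 (Summary) and 6.1 assign Arm A by whether matched therapy was received, not by the actionability label. If the exit is enforced, the patient stays in the denominator and cannot enter the numerator. If it is not, a patient treated in a local matched trial can still count as matched.

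**Size, by assumption.** Let s be the second site's share of patients and q the share of its patients whose only matched option is a trial at their own site and not at UCSD. The protocol gives neither. The downward shift in the study-wide actionable proportion is s × q, and within the second site it is q. With the 1150 evaluable patients of Section 3.8:

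| s | q = 1% | q = 5% | q = 10% |
|---|---|---|---|
| 10% | 0.1 points (about 1 patient) | 0.5 (about 6) | 1.0 (about 12) |
| 25% | 0.25 (about 3) | 1.25 (about 14) | 2.5 (about 29) |
| 50% | 0.5 (about 6) | 2.5 (about 29) | 5.0 (about 58) |

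For example, 0.25 × 0.05 = 0.0125, and 1150 × 0.0125 ≈ 14. The shift within the second site is 1 to 10 points.

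For scale, Section 3.2 expects 50 to 70% of patients to have potentially actionable alterations. The 95% half-width is 1.96 × √(p(1−p)/1150): 2.9 points at p = 0.5, 2.8 at 0.6 and 2.6 at 0.7. Only the corner s = 50%, q = 10% exceeds it.

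This sum covers row 2 for second-site patients only. It leaves out UCSD patients whose only trial is elsewhere, and any second-site patients who count as actionable solely through a UCSD trial.

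**The case against.** The strongest case against is that few patients, perhaps none, are touched. The approved-drug route covers any tumor type at every site. Section 3.2 describes the process as still evolving and relies on expert opinion, so the Board may not apply the UCSD limit literally. One trial list for everyone also has a merit: the same alteration gets the same class at both sites, whereas counting only the enrolling site's trials would tie the endpoint to each site's portfolio. No between-site comparison is planned.

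Most of this stands as a limit on size. It does not remove the contradiction. The limit is written into both definitions. The protocol names Avera separately where rules differ (Sections 2.1, 2.2, 4.1 and 5.4.4), so UCSD cannot safely be read as shorthand for the patient's own site.

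Three stronger readings are tempting but not supported:

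- A reader might infer that the second site's patients in general are misclassified, or that the error occurs only there. The approved-drug route rules out the first; row 3 of the comparison rules out the second.
- A reader might infer that second-site patients are wrongly called actionable because UCSD trials are out of their reach. The protocol does not say that they cannot join those trials.
- A reader might set the shift against the 40% success criterion in Section 5.1, and note that losing one of the expected 30 matched among 75 gives 29/75 = 38.7%. That criterion concerns receipt of matched therapy, not actionability. The loss would need the exit to be enforced on a patient who would otherwise have been matched, and nothing shows that such a patient exists.

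**Conclusion.** The point holds as an internal contradiction with a limited effect. As written, the classification gives the wrong label to patients who have no approved drug in any tumor type and whose only matched trial is not at UCSD. This lowers the third secondary endpoint and can end their participation early.

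The size rests wholly on the assumed s (10 to 50%) and q (1 to 10%), which give 0.1 to 5 points study-wide and 1 to 10 points within the second site. In most of that range the study-wide shift is smaller than the sampling error. An effect on the primary endpoint is conditional on the Section 1.2 exit being enforced despite the treatment described in Section 3.2. No sample size, power or threshold in the protocol is wrong because of this wording.

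**What to change.** In both definitions in Section 3.2, C, replace the reference to UCSD with wording that covers the second site and agrees with the matching rule, for example: at a participating site, or another trial accessible to the patient. Naming only the enrolling site would leave the mismatch with Sections 1.2 and 3.2 for trials open elsewhere.

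Reconcile Section 1.2 with Section 3.2 (Molecular Matching and Molecular Tumor Board/Study Committee), so that it is clear whether patients with no actionable alterations leave the study and what data are kept on them.

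Re-check patients already classed as non-actionable, and those classed as actionable only through a UCSD trial, so that one definition applies throughout. Reporting the actionable proportion by site as well would show whether the wording mattered.

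The text change is short and needs no new patients. The cost is the re-check: Section 7.4 records auditing since 2016 and a change in 2020, so classifications are likely to exist already. It should be small, because patients with an approved-drug route need no review.

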### **FDA-approved Companion Diagnostics**

The current study will perform tumor molecular profiling through FoundationOne™ to navigate patients to a matched therapy. For those patients with an actionable tumor alteration identified by the FoundationOne™ assay, we will determine if an FDA-approved companion diagnostic test exists and is indicated for the patient based upon their malignancy (**Tables 1 and 2**). Appropriate companion diagnostic test(s) will be performed for the patient, along with any other clinically indicated standard of care laboratory tests (e.g., CEA for colorectal cancer and CA-19-9 for pancreas cancer). If there is a discrepancy between results of FoundationOne™ next generation sequencing and the FDA-approved test, the FDA-approved test results will supersede. For those patients with an actionable tumor alteration that is confirmed by a corresponding companion diagnostic test, matched therapy will be recommended by the Study Committee (or Molecular Tumor Board) from either FDA-approved drugs or matched agents under investigation in a separate clinical trial. Those patients, for whom there are no available matched treatments, will serve as the unmatched therapy controls. All final treatment decisions are the responsibility of the treating physician.

**Table 1. Companion Diagnostic Tests: *In vitro* and Imaging Tools**

(<http://www.fda.gov/MedicalDevices/ProductsandMedicalProcedures/InVitroDiagnostics/ucm301431.htm>; April 18, 2014)

| Drug Trade Name
(Generic Name)                 | NDA/BLA                         | Test Trade Name                    | PMA                      | Test Manufacturer                                | Intended Use (IU)/ Indications for Use (IFU)                                                                                                                                                                                                                                                                                                                                                                                                                                                                                                                                                                                                                                                                                                                                                                                                                                                         |
|---------------------------------------------------|---------------------------------|------------------------------------|--------------------------|--------------------------------------------------|------------------------------------------------------------------------------------------------------------------------------------------------------------------------------------------------------------------------------------------------------------------------------------------------------------------------------------------------------------------------------------------------------------------------------------------------------------------------------------------------------------------------------------------------------------------------------------------------------------------------------------------------------------------------------------------------------------------------------------------------------------------------------------------------------------------------------------------------------------------------------------------------------|
| Erbix
(cetuximab)                              | BLA
125084                   | therascreen
KRAS RGQ
PCR Kit | P110030                  | Qiagen
Manchester,
Ltd.                    | The therascreen KRAS RGQ PCR Kit is a real-time qualitative PCR assay used on the Rotor-Gene Q MDx instrument for the detection of seven somatic mutations in the human KRAS oncogene, using DNA extracted from formalin fixed paraffin-embedded (FFPE) colorectal cancer (CRC) tissue. The therascreen KRAS RGQ PCR Kit is intended to aid in the identification of CRC patients for treatment with Erbix (cetuximab) based on a KRAS no mutation detected test result.                                                                                                                                                                                                                                                                                                                                                                                                               |
| Erbix
(cetuximab)
Vectibix
(panitumumab) | BLA
125084;
BLA
125147 | DAKO EGFR
PharmDx Kit           | P030044
S001-
S002 | Dako North
America, Inc.                      | The EGFR pharmDx™ assay is a qualitative immunohistochemical (IHC) kit system to identify epidermal growth factor receptor (EGFR) expression in normal and neoplastic tissues routinely-fixed for histological evaluation. EGFR pharmDx specifically detects the EGFR (HER1) protein in EGFR-expressing cells.

EGFR pharmDx is indicated as an aid in identifying colorectal cancer patients eligible for treatment with Erbix (cetuximab) or Vectibix (panitumumab).                                                                                                                                                                                                                                                                                                                                                                                                                         |
| Exjade
(deferasirox)                           | NDA
021882                   | Ferriscan                          | K124065                  | Resonance
Health Analysis
Services Pty Ltd | The FerriScan R2-MRI Analysis System is intended to measure liver iron concentration to aid in the identification and monitoring of non-transfusion dependent thalassemia patients receiving therapy with deferasirox.                                                                                                                                                                                                                                                                                                                                                                                                                                                                                                                                                                                                                                                                               |
| Gilotrif
(afatinib)                            | NDA
201292                   | therascreen
EGFR RGQ
PCR Kit | P120022                  | Qiagen
Manchester,
Ltd.                    | The therascreen EGFR RGQ PCR Kit is a real-time PCR test for the qualitative detection of exon 19 deletions and exon 21 (L858R) substitution mutations of the epidermal growth factor receptor (EGFR) gene in DNA derived from formalin-fixed paraffin-embedded (FFPE) non-small cell lung cancer (NSCLC) tumor tissue. The test is intended to be used to select patients with NSCLC for whom GILOTRIF (afatinib), an EGFR tyrosine kinase inhibitor (TKI), is indicated. Safety and efficacy of GILOTRIF (afatinib) have not been established in patients whose tumors have L861Q, G719X, S768I, exon 20 insertions, and T790M mutations, which are also detected by the therascreen EGFR RGQ PCR Kit. Specimens are processed using the QIAamp DSP DNA FFPE Tissue Kit for manual sample preparation and the Rotor-Gene Q MDx instrument for automated amplification and detection. |
| Gleevec/Glivec
(imatinib
mesylate)          | NDA
021335;
NDA
021588 | DAKO C-KIT
PharmDx              | P040011
S001-
S002 | Dako North
America, Inc.                      | The c-Kit pharmDX assay is a qualitative immunohistochemical (IHC) kit system used on the Dako Autostainer, for the identification of c-kit protein/CD 117 antigen (c-kit protein) expression in normal and neoplastic formalin-fixed paraffin-embedded tissues for histological evaluation. The c-Kit pharmDX rabbit polyclonal antibodies specifically detect the c-kit protein in CD 117 antigen-expressing cells.

The c-Kit pharmDx is indicated as an aid in the differential diagnosis of gastrointestinal stromal tumors (GIST). After diagnosis of GIST, results from c-Kit pharmDx may be used as an aid in identifying those patients                                                                                                                                                                                                                                               |

| Drug Trade Name
(Generic Name) | NDA/BLA       | Test Trade Name                                                                    | PMA                      | Test Manufacturer                   | Intended Use (IU)/ Indications for Use (IFU)                                                                                                                                                                                                                                                                                                                                                                                                                                                                                                                                                                                                                                                                                                                                                                                                                               |
|-----------------------------------|---------------|------------------------------------------------------------------------------------|--------------------------|-------------------------------------|----------------------------------------------------------------------------------------------------------------------------------------------------------------------------------------------------------------------------------------------------------------------------------------------------------------------------------------------------------------------------------------------------------------------------------------------------------------------------------------------------------------------------------------------------------------------------------------------------------------------------------------------------------------------------------------------------------------------------------------------------------------------------------------------------------------------------------------------------------------------------|
|                                   |               |                                                                                    |                          |                                     | eligible for treatment with Gleevec/Glivec (imatinib mesylate). Results from hematoxylin and eosin (H&E) stains and a panel of antibodies can aid in the differential diagnosis of GIST. Interpretation must be made by a qualified pathologist, within the context of a patient's clinical history, proper controls, and other diagnostic tests.                                                                                                                                                                                                                                                                                                                                                                                                                                                                                                                          |
| Herceptin
(trastuzumab)        | BLA
103792 | INFORM
HER-2/NEU                                                                | P940004
S001          | Ventana
Medical
Systems, Inc. | The Inform Her-2/Neu gene detection system is a fluorescence in situ hybridization (FISH) DNA probe assay that determines the qualitative presence of Her-2/Neu gene amplification on formalin-fixed, paraffin embedded human breast tissue as an aid to stratify breast cancer patients according to risk for recurrence or disease-related death. It is indicated for use as an adjunct to existing clinical and pathologic information currently used as prognostic indicators in the risk stratification of breast cancer in patients who have had a priori invasive, localized breast carcinoma and who are lymph node-negative.                                                                                                                                                                                                                                      |
| Herceptin
(trastuzumab)        | BLA
103792 | PATHVYSION
HER-2 DNA
Probe Kit                                               | P980024
S001-
S010 | Abbott Molecular
Inc.            | The PathVysion HER-2 DNA Probe Kit (PathVysion Kit) is designed to detect amplification of the HER-2/neu gene via fluorescence in situ hybridization (FISH) in formalin-fixed, paraffin-embedded human breast cancer tissue specimens. Results from the PathVysion Kit are intended for use as an adjunct to existing clinical and pathologic information currently used as prognostic factors in stage II, node-positive breast cancer patients. The PathVysion Kit is further indicated as an aid to predict disease-free and overall survival in patients with stage II, node positive breast cancer treated with adjuvant cyclophosphamide, doxorubicin, and 5-fluorouracil (CAF) chemotherapy. The Pathvysion Kit is indicated as an aid in the assessment of patients for whom herceptin (trastuzumab) treatment is being considered (see herceptin package insert). |
| Herceptin
(trastuzumab)        | BLA
103792 | PATHWAY
ANTI-HER-
2/NEU (4B5)
Rabbit
Monoclonal
Primary
Antibody | P990081
S001-
S016 | Ventana
Medical
Systems, Inc. | Ventana Medical Systems' PATHWAY Her2 (clone CB11) is a mouse monoclonal antibody intended for laboratory use for the semi-quantitative detection of c-erbB-2 antigen in sections of formalin-fixed, paraffin-embedded normal and neoplastic tissue on a Ventana automated immunohistochemistry slide staining device. It is indicated as an aid in the assessment of breast cancer patients for whom Herceptin treatment is being considered.                                                                                                                                                                                                                                                                                                                                                                                                                             |
| Herceptin
(trastuzumab)        | BLA
103792 | INSITE HER-
2/NEU KIT                                                           | P040030                  | Biogenex
Laboratories,
Inc.   | InSite Her-2/neu Mouse Monoclonal Antibody (Clone C1B11) kit is intended for In Vitro Diagnostic use in Immunohistochemistry (IHC) assays to semi-quantitatively localize by light microscopy the over-expression of Her-2/neu (i.e., c-erbB-2) in formalin-fixed, paraffin-embedded normal and neoplastic tissue sections. InSite Her-2/neu is indicated as an aid in the assessment of breast cancer patients for whom Herceptin (Trastuzumab) therapy is being considered. Clinical interpretation of InSite Her-2/neu immunostaining results (absence or presence; semi-quantitative intensity score) should be complemented by appropriate controls and morphological tissue analysis and be evaluated by a qualified pathologist within the context of patient clinical history and other diagnostic results.                                                        |

